#### **Establishment of an organoid bank**

Over the past 10 years, a large number of studies have contributed to the evolution of cancer modeling systems, from the traditional two-dimensional cancer cell culture system to more complex three-dimensional (3D) models. Because of this, we now know that a tumor is not just a simple mass of cancerous cells that proliferate, but rather is a complex tissue composed of a dynamic extracellular matrix with a stromal component and immune and endothelial cells. Significant efforts are currently being made to better recapitulate the tumor microenvironment, as well as discussing the potential of tumor engineering. These approaches include the development of modified matrices and 3D co-cultures to reproduce the complexity of tumor-stroma interactions in vitro and are the first step towards ex-vivo tumor modeling.

Starting from tumor stem cells, it is now possible to generate tumor organoids that better recapitulate certain aspects of the original tumor, much more so than in simple 2D cultures, as well as more quickly (< 1 month) and with greater efficiency (> 75% regardless of tumor subtype) than xenograft models. Therefore, generating organoids from tumors could be a very relevant alternative, making it possible to amplify tumor material in order to generate a bank of tumor organoids in sufficient quantity, at a lower cost, and within a timeframe compatible with trials of therapeutic molecules, such as in a personalized medicine study like the Permed study.

#### **Study design:**

First, familiarization with generating breast tumor organoids, all subtypes:

- 1- Establishment of one or more environments suitable for different sub-types of breast cancer:
  - a. Analyses performed on patient tumors amplified beforehand from xenografts.

- b. Validation in patients included prospectively.
- 2- Establishment of a growth (monitoring the growth of generated organoids) and heterogeneity score:
  - a. Rate
  - b. Shape
  - c. Survival and passages, presence of stem cells
- 3- Comparison with the existing xenograft model, taking into account the subtypes and similarity to the initial tumor.
- 4- Presence or not of mutations identified in the tumor.
- 5- Evaluation of using organoids for functional tests; study of the tumor microenvironment, testing targeted therapies (antibodies, etc.), evaluating metastatic potential (quantification of the strain's potential, migratory capacities, invasive properties, etc.).

Secondly, the creation of a breast cancer organoid bank (frozen organoids). This bank can be used to carry out functional analyses of well-characterized tumors and analyses involving targeted therapies may also be developed.

#### Assessment of therapeutic response

After obtaining and expanding the xenograft, the mutational status will be assessed as well as the status of the patient's tumor sample.

The tumor cells obtained via the mouse model will be cultivated in vitro for a study of therapeutic responsiveness as a "short-term culture".

These cells will then be exposed in vitro for 96 hours to a panel of drugs containing nearly 50 molecules including chemotherapies, targeted therapies, and innovative products.

The drugs considered to be "active" in vitro will be validated in vivo, in mice.

Additional analyses based more specifically on treatment effectiveness in cancer stem cells, as well as identifying anti-CSC treatments, could be carried out using this model.

## **Appendix 4: Study of circulating tumor DNA**

Tumor development is often accompanied by increased levels of tumor DNA circulating in the blood.

In this context, the release of DNA into the bloodstream may be caused by the primary tumor, circulating tumor cells, distant micrometastases, and normal cells such as hematopoietic and stromal cells (28). While this circulating tumor DNA can now be detected, its usefulness as a non-invasive diagnostic biomarker ("liquid biopsy") reflecting the characteristics of the primary tumor and micrometastases remains to be demonstrated.

Our study aims to assess the interest and feasibility of sequencing circulating tumor DNA compared to sequencing tumor samples.

The presence of circulating tumor DNA will be evaluated from the plasma obtained from the 4 blood tubes in EDTA.

The tubes will be centrifuged at 800g for 10 minutes. The plasma will then be aliquoted and frozen in cryotubes at -80°C.

When thawing a series of samples, the following protocol will be adhered to:

- Centrifugation at 20,000g for 10 minutes.
- Recovery of the supernatant and addition of 200 µL of Proteinase K.
- Addition of the ACL buffer containing the RNA carrier.
- Incubation for 30 minutes at 60°C.
- Addition of 3 ml of ACB buffer to the lysate - vortex 30 seconds.
- 5 minutes in ice.
- Depositing of the lysate in extension tubes for the QIAamp column on the QIA Vac 24 Plus vacuum system.
- Creation of a vacuum (800 mbar).
- Once the column is dry, addition of washing buffer 1, then buffer 2, then pure ethanol.
- Once the column is dry, centrifugation at 20,000g for 3 minutes.
- Drying of the column for 10 minutes at 56°C.
- Application of the elution buffer, and after 5 minutes, centrifugation for 1 minute at 20,000g for nucleic acid elution.

The molecular analyses will be carried out under the same conditions as those described in the protocol (section 4.4-molecular analyses).

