#### 4.2.2 – Blood samples

To definitively identify somatic alterations, it is necessary to compare the genome of cancer cells with that of normal cells (e.g. leukocytes) from the same patient. In addition, an analysis of circulating tumor DNA and circulating tumor cells may be performed as part of ancillary studies described in the appendices (Appendices 4 and 5).

For each patient there will be taken, preferably upon inclusion during a check-up, biopsy, or initial visit to an operating room (examination under anesthesia, diagnostic or therapeutic surgical procedure), 5 tubes each with 4 ml of blood in EDTA, i.e. 20 ml of blood for the extraction of DNA from normal cells and analyses of circulating tumor DNA (Appendix 4).

The tubes will be sent to the CRB within 2 hours for centrifugation (at 800G for 10 minutes at 4 °C) and aliquoting (plasma cryotubes for the study of circulating tumor DNA and pellet for DNA extraction) followed by frozen storage. In the event of a relapse during study follow-up, a new blood sample (5 tubes of 4 ml blood in EDTA) may also be taken for analysis of circulating tumor DNA.

Specifically, in cases of patients with breast cancer or cancer of the digestive tract:

As part of the complementary study of circulating tumor cells described in Appendix 5, an additional sample of 5 tubes of 4 ml of blood in EDTA, i.e. an additional 20 ml, will be collected exclusively in patients suffering from locally advanced or metastatic breast cancer or metastatic digestive cancer. The total volume of blood drawn from these patients will be 40 ml.

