| 
Biopsy
(Sampling limited to 5 fragments per target and to a total of 10 fragments maximum, all targets combined)
 
or
 
Surgical specimen
 | 
Send to the Pathology Department within 2 hours.
At least 3 fragments, in order of priority:
 
 
- A fragment, after verification of tumor cellularity, to be frozen for the imminent extraction of nucleic acids.
 
- A fragment fixed and embedded in paraffin for complementary immunohistochemical or biological studies.
 
- At least one fragment, after verification of tumor cellularity, to be frozen for use in subsequent molecular studies of proteomics and/or genomics.
 
 |
| Blood samples                                                                                                                                           |                                                                                                                                                                                                                                                                                                                                                                                                                                                                                                                                                              |
| 
5 tubes of 4 ml blood in EDTA, i.e. 20 ml to obtain the genome of normal cells and to perform analyses on circulating tumor DNA.
                        | 
Send to Biological Resource Center within 2 hours.
 
Centrifuge: 800G for 10 minutes at 4°C. Separate:
 
 
- the pellet
 
 
Freeze the dried pellet for nucleic acid extraction.
 
 
- the plasma
 
 
Aliquot in cryotubes and store at -80°C for analyses of circulating tumor DNA.
                                                                                                                                                           |

| Supplementary samples                                                                                             |                                                                                                                                                                                                                                                              |

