| 
Biopsy
(Sampling limited to 5 fragments per target and a maximum of 10 fragments total, all targets combined)
 | 
Send to Pathology Department within 2 hours.
At least 3 fragments, in the following order of priority:
 
 
- A fragment, after verification of tumor cellularity, to be frozen for the imminent
 
     |

|                                                                                |                                                                                                                                                                                                                                                                                                                                                               |
|--------------------------------------------------------------------------------|---------------------------------------------------------------------------------------------------------------------------------------------------------------------------------------------------------------------------------------------------------------------------------------------------------------------------------------------------------------|
| or

Surgical specimen                                                    | 
extraction of nucleic acids.
 
 
- A fragment fixed and embedded in paraffin for complementary immunohistochemical or biological studies.
 
- At least one fragment, after verification of tumor cellularity, to be frozen for use in subsequent molecular studies of proteomics and/or genomics.
 
 |
| 5 tubes of 4 ml in EDTA (20 ml total) for analyses of circulating tumor cells. | 
Send to Biological Resource Center within 2 hours.
 
Centrifuge: 800G for 10 minutes at 4°C.
 
Aliquot in cryotubes and store at -80°C for analyses of circulating tumor DNA.
                                                                                                                                                                |

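### Plasma for circulating tumor DNA gets its high-speed spin only after thawing, so DNA from residual blood cells can dilute tumor allele fractions by an amount the protocol neither limits nor measures

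*Protocol*

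**What the plan says.** Appendix 4 sets out the ctDNA handling in sequence. First, "The tubes will be centrifuged at 800g for 10 minutes". Then, "The plasma will then be aliquoted and frozen in cryotubes at -80°C". The extraction steps follow under the words "When thawing a series of samples, the following protocol will be adhered to", and the first of them is "Centrifugation at 20,000g for 10 minutes". The supernatant from that spin is what goes forward to proteinase digestion and extraction.

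The other places that describe this plasma agree:

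- Section 4.2.2: "The tubes will be sent to the CRB within 2 hours for centrifugation (at 800G for 10 minutes at 4 °C) and aliquoting", followed by frozen storage.
- Appendix 2, inclusion and relapse rows: "Centrifuge: 800G for 10 minutes at 4°C", and then "Aliquot in cryotubes and store at -80°C for analyses of circulating tumor DNA".

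None of them adds a second spin before freezing. None sets a limit on cell carry-over or a check for contaminating genomic DNA. Appendix 4 does recognise normal cells as contributors to DNA in blood; its list of sources ends with "distant micrometastases, and normal cells such as hematopoietic and stromal cells".

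The stated purpose of the ancillary study is to judge the interest and feasibility of sequencing ctDNA against sequencing tumor samples, using the same molecular methods as section 4.4. Section 2.2 lists ctDNA analysis among the secondary objectives.

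**The concern.** The protocol already contains a high-speed clearing spin but places it after the freeze. Before the freeze, an intact blood cell left in the plasma can be pelleted and discarded. If that cell breaks on freezing or thawing, its DNA is in solution and stays in the supernatant that Appendix 4 recovers.

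Such DNA is not tumor DNA. It raises the denominator of the allele fraction and leaves the tumor-derived numerator unchanged, so the error has one direction: fractions fall and some variants are missed. How far they fall depends on how cleanly each tube was handled, not on the patient's disease.

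At stake is the reading of the ancillary study. If agreement between plasma and tissue is poor, the sponsor could not say whether ctDNA carries too little information or the handling diluted it. DNA released inside a stored aliquot cannot be taken out later. The matched leukocyte DNA of section 4.2.2 helps to separate germline from somatic variants but does not restore a lowered allele fraction.

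**Working it through.** **Step 1: order of handling.** Set side by side, the protocol gives:

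| Place | Before freezing | After thawing |
|---|---|---|
| Section 4.2.2 | 800g, 10 min, 4 °C | not described |
| Appendix 2, inclusion | 800g, 10 min, 4 °C | not described |
| Appendix 2, relapse | 800g, 10 min, 4 °C | not described |
| Appendix 4 | 800g, 10 min | 20,000g, 10 min, supernatant kept |

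The descriptions are consistent, so the order is the procedure as fixed and not a slip in one table.

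**Step 2: stated figure.** There is none to reproduce. The protocol gives no residual cell count, plasma DNA yield, expected allele fraction or detection limit for plasma.

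**Step 3: scale, under assumptions.** All inputs here are assumptions:

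- DNA per residual nucleated cell: 6.6 pg
- every residual cell lyses and all its DNA stays in the supernatant
- true plasma DNA, c: 5, 10 or 30 ng/ml
- residual cells, n: 10 to 5,000 per ml of plasma

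Added DNA (ng/ml) = n × 0.0066

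Share of the true allele fraction retained = c / (c + n × 0.0066)

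| n per ml | Added DNA, ng/ml | c = 5 | c = 10 | c = 30 |
|---|---|---|---|---|
| 10 | 0.066 | 98.7% | 99.3% | 99.8% |
| 100 | 0.66 | 88.3% | 93.8% | 97.8% |
| 1,000 | 6.6 | 43.1% | 60.2% | 82.0% |
| 5,000 | 33 | 13.2% | 23.3% | 47.6% |

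For example, at 1,000 cells/ml and c = 5: 5 / (5 + 6.6) = 0.431. At 5,000 cells/ml and c = 30: 30 / (30 + 33) = 0.476.

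**Step 4: where the effect becomes material.** The allele fraction is halved when the added DNA equals c, that is when n = c / 0.0066. This gives 5 / 0.0066 = 758 cells/ml at the low end and 30 / 0.0066 = 4,545 cells/ml at the high end. A loss of one tenth needs n = (c / 9) / 0.0066, which is 84 cells/ml at c = 5 and 505 cells/ml at c = 30.

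The effect therefore runs from nothing of note to a severe loss, and the protocol gives no figure that places it in this range.

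**The case against.** The strongest reply is that the harm is not shown in the protocol. No passage contradicts another here and no stated number is wrong. For the dilution to matter, enough cells must survive the 800g spin, they must break on freezing, and the true plasma DNA must be low. The protocol is silent on the first and third. The second is general laboratory knowledge. All of this stands, and it is why the point is put as a risk.

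The protocol also has partial safeguards: delivery within 2 hours, a cold first spin, and a 20,000g spin before the digestion step, which removes cells still intact at that stage. These reduce the problem. They do not reach DNA already in solution.

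The ctDNA work is ancillary and aims at feasibility. No allele-fraction endpoint, sensitivity threshold or inclusion-versus-relapse comparison is fixed, and relapse sampling is optional. That stands too and keeps the severity low.

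Finally, changing the procedure partway can do its own damage. Section 6.2 refers to a fourth substantial modification that raises the total from 460 to 560 patients, so samples may already be banked. Inclusion plasma would then be mostly single-spin and relapse plasma double-spin. Processing version would be confounded with time point, and a covariate for version could not cleanly separate the two. The fix has to deal with this.

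Two stronger inferences are tempting and should not be drawn:

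- A reader might infer that the stored plasma is certainly and badly diluted. Nothing in the protocol establishes that; at 10 residual cells/ml the loss would be about 1% or less.
- A reader might infer that keeping the cell pellet for normal DNA makes carry-over more likely. What is done with the pellet afterwards does not change how many cells came across with the plasma.

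**Conclusion.** The point holds as a conditional risk of low severity. Followed as written, the protocol freezes plasma after one low-speed spin and applies the clearing spin where it can no longer remove DNA already released. The direction of any bias is known: toward lower allele fractions and missed variants in the comparison with tumor tissue. Its size is not known. Under the assumptions above (6.6 pg per cell, full lysis, 5 to 30 ng/ml plasma DNA), the retained share runs from about 99-100% at 10 residual cells/ml to 13-48% at 5,000.

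The primary objective and the sample size rest on tumor samples and are untouched.

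**What to change.** **Handling.** In section 4.2.2, in both plasma rows of Appendix 2 (inclusion and relapse) and in Appendix 4, state that the plasma separated by the 800g spin is spun again at 20,000g for 10 minutes, and only then aliquoted and frozen. Keep the existing spin after thawing.

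**Data and analysis.** Record the processing version for each sample. Report concordance between ctDNA and tumor by version. Restrict any inclusion-versus-relapse comparison to pairs processed in the same way. For a patient whose inclusion plasma had a single spin, keep one single-spin aliquot at relapse alongside the double-spin one, so that a matched pair exists. Such split samples would also show directly how much the extra spin changes the allele fraction.

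**Cost.** One additional 10-minute spin at sample reception, using a force and duration the protocol already specifies, plus text edits in the places named. The drawbacks are a little more work on receipt and a sample bank that holds two processing versions, which the recording and pairing rules above are meant to manage.

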## **Appendix 5: Study of circulating tumor cells**

Circulating tumor cells (CTCs) are exploding as a new major prognostic biomarker that could play an essential role in the implementation of targeted therapies for cancers and their metastatic evolution (29-31).

Although the existence of CTCs, as precursors of metastatic lesions, was suggested over 100 years ago, formal evidence that CTCs are indeed capable of initiating metastatic lesions has not been demonstrated due to major technical limitations that have hitherto prevented their precise genomic and phenotypic characterization (32, 33). Indeed, CTCs are rare events detected in approximately 20 to 50%, depending on the cancer, of metastatic patients (34). The detection of CTCs in the blood is associated with a poorer prognosis, reduced survival, may reflect an lack of treatment response (or a partial response that would target sensitive clones while resistant clones remain), or may even predict the non-resectability of a tumor in the cases of the most aggressive tumors (35-37).

CTCs as reflections of intratumoral clonal heterogeneity with invasive potential must be studied in order to improve their targeting, depending on their stage of development in tumorigenesis.

Our objectives for this study include:

- carrying out a preliminary study in order to demonstrate that we have, at the Paoli-Calmettes Institute, the tools necessary to further explore the characterization of these biomarkers.
- identifying molecular alterations on the purest CTC in parallel to the primary tumor and/or metastasis in order to assess intratumoral molecular heterogeneity and establish disrupted signaling pathways and potential therapeutic targets.

### **Pilot phase: Implementation of a new technique for isolating CTCs**

The isolation of CTCs is usually performed via the CellSearch® system, which is based on the epithelial cell marker anti-Epcam. However, CTCs decrease or lose the expression of this marker when passing into circulation, thus leading to an underestimation of the real number of circulating cells.

We propose here an original approach in two steps, utilizing a volume of 16 ml of blood in EDTA:

1. Enrichment by way of negative selection where all the hematopoietic cells are removed, leaving only those cells that are not usually found in the area.
2. Further purification of the previously enriched cells, including the detection of molecules associated with the mesenchymal-epithelial transition process, as well as new markers of carcinogenesis (MUC1, MUC4, etc.). These cells will be selected by flow cytometry, deep array (phenotyping/genotyping) or any other suitable technique, depending on the availability of the devices which are being/will be used. The purity of these cells will be assessed by evaluating the expression of transcripts of typical epithelial markers, such as cytokeratins.

The first part of this study will be carried out, initially, using samples obtained from:

- 20 patients with locally advanced breast cancer or, if the results of the approach are conclusive, all patients with breast cancer included in the PERMED01 study. In the absence of conclusive results, the study will be stopped.

–20 patients with digestive cancer (especially pancreatic cancer). Indeed, these cancers, by virtue of their clinical characteristics, appear to be good candidates for studying CTC detection sensitivity (38-41).

In the specific case of pancreatic cancer, two studies recently confirmed the prognostic role of CTCs (42, 43).

In addition, Kaifi et al. recently compared two different isolation techniques: CellSearch® (25 samples) and a filtration technique (16 samples), and demonstrated that CTCs are, in the majority of cases, undetectable with CellSearch® but almost always detectable using the filtration technique (44). We would like to assess the sensitivity limits of our detection tools, in particular our filtration technique, which is similar to that described by Kaifi et al. We hope to be able to detect CTCs in at least 10 patients.

#### Study of genomic, transcriptomic and mutator profiles (by array-CGH, transcriptome analysis, and NGS)

The objective of this program will ultimately be to obtain genomic, transcriptomic and mutator profiles (by array-CGH, transcriptome analysis, and NGS) from a virtually pure population of CTCs and/or a single cell. These analyses will be performed in the Molecular Oncology laboratory (UMR1068) using a targeted panel for analysis via high throughput sequencing data and/or transcriptomic data, in order to study the major genes involved in the tumor aggressiveness and drug susceptibility. These analyses will be carried out under the same conditions as those described in the protocol (section 4.4-molecular analyses).

